#### Preventive treatments during follow-up

After baseline visit is completed and MRI is performed, primary care physicians will receive a summary with the most relevant results for each participant. Family doctors will take care of vascular risk factor control, following their routine practice. As for silent brain infarcts, since at present there is no clear evidence of whether a secondary stroke prevention should be applied to these patients and until new information comes from randomized clinical trials, recommendations will be to optimize BP control in all cases as much as possible and considering start antiplatelet treatment and/or cholesterol-lowering drugs in cases with the estimated global vascular risk is high (≥10 score in the Framingham-calibrated REGICOR function) [1].

### Study outcome

The primary outcomes of this study are the determination of the prevalence of silent brain infarctions and other silent lesions (as described in the neuroimaging protocol) and the presence and time to first-ever stroke (fatal or non-fatal ischemic or hemorrhagic stroke) or TIA. Stroke will be defined clinically as a focal neurological deficit thought of vascular origin, lasting more than 24 hours and confirmed by clinical evaluation and the use of a brain CT scan or MRI. TIA will be defined according to the classical definition, as an acute focal neurologic deficit due to cerebral ischemia that resolves completely within 24 hours, regardless of neuroimaging findings.

Other cardiovascular events will be analysed as secondary events: coronary events (myocardial infarction, angina requiring hospitalization, coronary angioplasty or surgery); cardiac failure requiring admission to hospital; vascular complications (lower limbs, aorta or carotid arteries) requiring revascularization and vascular death.

Finally, cognitive decline will be evaluated as secondary end-point during follow-up.

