### Baseline visit and procedures

#### Inclusion and exclusion criteria

At inclusion visit, fulfilment of inclusion and exclusion criteria is re-assessed by investigators. Briefly, inclusion criteria consists on: 1)Patients with essential hypertension diagnosed at least one year earlier; 2) Age comprised between 50 and 70 years; 3) Patients who give their consent to participate in the study.

Patients are excluded when: 1) they have history of previous stroke or dementia; 2) Brain MRI is contraindicated; 3) there is a suspicion of white coat hypertension syndrome or 4) patients affected by a terminal illness preventing future follow-up examinations, based on the investigator criteria.

A particular effort is made to rule out the presence of a previous stroke, and for that purpose investigators are trained and an adaptation of the Stroke Symptom Questionnaire by Berger K and collaborators is used [9].

Likewise, when a suspicion of dementia appears, following DSM-IV-R criteria [10] the patient is not included in the study and a proper evaluation in the presence of a caregiver is therefore recommended.

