### Follow-up visits

The participants will be contacted yearly by phone, one and two years after the inclusion visit. They will be asked about BP control, appearance of new vascular risk factors, and the presence of stroke/TIA or new vascular events. In case of any event has occurred, this will be verified by checking clinical records from their family doctors and hospital records. Participants will also be asked about medical treatment adherence using the same questionnaire performed at baseline and treatment adverse events.

Finally, three years after inclusion a new visit is planned by the investigator’s team at the primary care center where the patient belongs, when data relative to new medical history and physical examination (blood pressure, height and weight and waist circumference measurement) will be collected, together with a new cognitive assessment with the Dementia Rating Scale-2.

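### The written stroke definition shuts out strokes that kill within 24 hours or before a scan, although the primary outcome includes fatal stroke

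*Protocol article*

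**What the plan says.** All the wording at issue is in the protocol article, mainly in the Study outcome section.

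- **Outcome.** Besides lesion prevalence, the primary outcomes include the presence of, and "time to first-ever stroke (fatal or non-fatal ischemic or hemorrhagic stroke) or TIA".
- **Stroke.** The next sentence defines stroke clinically, as a focal deficit of presumed vascular origin, "lasting more than 24 hours and confirmed by clinical evaluation and the use of a brain CT scan or MRI". Duration, clinical evaluation and imaging are joined by *and*.
- **TIA.** This is "an acute focal neurologic deficit due to cerebral ischemia that resolves completely within 24 hours, regardless of neuroimaging findings".
- **Secondary events.** The list of other cardiovascular events closes with vascular complications "requiring revascularization and vascular death".
- **Verification.** Under Follow-up visits, when an event has occurred, "this will be verified by checking clinical records from their family doctors and hospital records".
- **Analysis.** Statistical methods plans Cox proportional hazards models for stroke/TIA or further cardiovascular events.

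**The concern.** The outcome sentence says that fatal strokes count. The definition sentence sets conditions that the fastest fatal strokes cannot meet. It offers no alternative for a patient who dies before 24 hours have passed, and none for a patient who dies before CT or MRI.

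What is at stake is which events enter a primary outcome. The events left out are not a random subset, because they are the most severe strokes. Consistency is also at stake. An adjudicator who follows the definition will exclude such a death, while one who follows the outcome sentence will include it. The article does not say which sentence governs.

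**Working it through.** **The plan's own figure.** The only sample-size figure concerns prevalence: n = z² p(1 − p)/d², with p = 0.10, d = 0.02 and z = 1.96. This gives 864.33, rounded up to the stated 865. It does not depend on the stroke definition, so the point leaves the sample size untouched.

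**Applying the definitions.**

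| Case | Stroke: over 24 h? | Stroke: CT or MRI? | TIA: fully resolved within 24 h? | Where it can count |
|---|---|---|---|---|
| Fatal after 24 h, imaged | yes | yes | no | primary outcome |
| Fatal within 24 h, imaged | no | yes | no | vascular death only |
| Fatal after 24 h, never imaged | yes | no | no | vascular death only |
| Fatal within 24 h, never imaged | no | no | no | vascular death only |

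A haemorrhage also fails the TIA definition because that definition requires ischaemia. The waiver of imaging findings belongs to the TIA definition alone, so it does not help an unimaged stroke.

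**Effect in the Cox model.** With stroke/TIA as the event, a death that is not classified as stroke ends follow-up without an event. In an ordinary Cox analysis that is censoring at death.

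**Size, by assumption.** The article gives neither a stroke/TIA rate nor the share of events that are rapidly fatal or unimaged. Assume 1000 participants, three years, an annual rate r of 0.5 to 1.5%, and a share s of 2 to 10% of all stroke/TIA events.

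- Events = 1000 × [1 − (1 − r)³]: 14.9 at r = 0.005, 29.7 at r = 0.01, 44.3 at r = 0.015.
- Events lost = events × s: lowest 14.9 × 0.02 = 0.3; middle 29.7 × 0.05 = 1.5; highest 44.3 × 0.10 = 4.4.

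The base includes TIAs, which by definition cannot be early deaths. Therefore s must be read as a share of strokes and TIAs together, and the upper end is generous.

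**Effect on power, by assumption.** Take a hazard ratio of 3 and 10% of participants with a silent infarct (the plan's expected prevalence). Power = Φ(√(events × 0.1 × 0.9) × ln 3 − 1.96). At s = 10%:

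- 14.9 events: power falls from 0.246 to 0.226.
- 44.3 events: power falls from 0.593 to 0.548.

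The loss of power is modest even at the largest assumed share. The problem is which events are removed more than how many.

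**The case against.** The strongest reply is that the intent is plain. The same paragraph names fatal stroke, so a sensible adjudicator would count a rapidly fatal one, and the handling of unimaged deaths is a detail that a journal article may leave to the full protocol. Requiring imaging is also a legitimate choice in favour of specificity. And a death excluded from the primary outcome is not lost to the study, since vascular death is collected as a secondary event.

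Part of this stands. Intent is indeed clear, the secondary list does limit the harm, and the number of events is probably small. But the article does not leave the definition open. It states one, and that definition conflicts with the sentence before it. Record checking under Follow-up visits supplies no rule for a fatal event without a scan. Counting such a death as secondary still leaves it out of the primary outcome.

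A reader might also infer two stronger points that the article does not support.

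- **That the hazard ratio for silent infarcts is materially biased.** The article gives no early-fatal share and nothing on how early deaths divide between participants with and without infarcts. Neither the size nor the direction of a bias can be derived.
- **That participants with a previous TIA are wrongly treated as event-free.** The exclusion criterion is that "they have history of previous stroke or dementia", and TIA is not named. However, *first-ever* can be read as qualifying stroke alone. The baseline interview also includes a stroke-symptom questionnaire and directed questions on established cardiovascular disease, so the article does not show that prior TIA goes unrecorded.

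**Conclusion.** The point holds as an internal conflict in the primary outcome. As written, a stroke fatal within 24 hours or before imaging meets neither the stroke nor the TIA definition, and no other section of the article repairs this. Fatal strokes that last longer than 24 hours and are imaged still count, so the gap is confined to early or unimaged deaths.

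That the gap exists follows from the text alone. Its size rests entirely on the assumed event rates and shares: from under one event to a few. It is worth correcting because the loss is selective, the expected event count is low under those assumptions, and the correction is simple. It does not call the design or the sample size into question.

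**What to change.** Reconcile the definition with the stated outcome in two steps.

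1. Make the duration requirement read *lasting more than 24 hours or leading to death*.
2. Keep CT or MRI as the standard confirmation. Where death came before imaging, allow confirmation from the family-doctor and hospital records already consulted, or from a death certificate if one is available.

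The cost is a short change of wording and a classification rule for the few cases concerned. Death certificates are not among the sources that the article lists, so using them adds a small step. No visit, scan or change in sample size is needed.

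The downside is that some fatal strokes will be classified with less certainty. Flag those confirmed without imaging, and report the stroke/TIA Cox analysis with and without them.

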#### Physical examination and vascular testing

Regarding physical examination, some measures are taken and recorded such as height, weight, waist circumference and BP (mean of the last two out of three measurements after five minutes rest).

Plus, a standard 12-lead ECG is performed to assess for signs of left ventricular hypertrophy (single measurement of R wave in aVL [16]) and heart rhythm disorders.

Afterwards, vascular testing is performed with the Vicorder™ device (Skidmore Medical Ltd, Bristol, UK). The Vicorder™ is small, portable, non-invasive and non-operator dependent device suited for use in community based studies [17]. This system provides two BP measurement channels and two Photoplethysmography (PPG) channels for the measurement of blood flow.

Briefly, two measurements are taken for each patient: carotid-femoral pulse wave velocity (cf-PWV) and the ankle-brachial index (ABI).

Cf-PWV is measured as the best approximation of aortic pulse wave velocity (aPWV), a marker of arterial stiffness. For the measurement, the patient should be resting in a supine position, with the head and shoulders raised by about 30 degrees allowing venous return from the brain and avoiding signal contamination by the Jugular vein. A neck-pad should be placed at the lower centre part of the Right Common Carotid Artery as tightened as possible without discomforting the patient. A distal BP cuff should be located on the ipsilateral upper thigh, as high to the groin as possible. The neck-pad and thigh cuff are inflated by the Vicorder to 60 mmHg and then deflated to obtain a pressure tracing. Cf-PWV is calculated by the Vicorder by comparing carotid and femoral pressure tracings after a stable pattern is obtained. Then, cf-PWV is defined as the ratio of the distance between the carotid and the thigh position and the time it takes for the pulse wave to travel from the proximal to the distal locations. For anatomical reasons, the distance between suprasternal notch and the centre of femoral cuff is chosen as the best estimation of the distance between the two arterial sites.

ABI is measured according to the current guidelines of the American Heart Association for each side as the ratio of the highest systolic BP of each ankle and the highest systolic BP of both upper limbs [18]. The lowest of the right and left ABI values will be used.

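### The secondary cardiovascular endpoint counts procedures that doctors decide on, and those doctors receive the baseline findings tested as predictors, so disclosure could shift the associations in either direction

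*Protocol article*

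**What the plan says.** Three parts of the protocol article meet here.

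- **Outcome.** Study outcome states that "Other cardiovascular events will be analysed as secondary events". The list includes "coronary events (myocardial infarction, angina requiring hospitalization, coronary angioplasty or surgery", then heart failure admission, and "vascular complications (lower limbs, aorta or carotid arteries) requiring revascularization and vascular death". Clinical events and procedures stand side by side in one group.
- **Disclosure.** Preventive treatments during follow-up states: "After baseline visit is completed and MRI is performed, primary care physicians will receive a summary with the most relevant results for each participant". After that, "Family doctors will take care of vascular risk factor control, following their routine practice". The contents of the summary are not itemised.
- **Predictors.** The Abstract gives, as the reason for measuring other organ damage (ABI included), the wish to establish what it contributes to later vascular events. Statistical methods plans a Cox model for predictors of stroke/TIA or further cardiovascular events, adjusted for variables with p < 0.1 on univariate testing.

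Follow-up visits adds that reported events are checked against family-doctor and hospital records. The article states blinding only for the MRI readers.

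**The concern.** A myocardial infarction or a vascular death happens whether or not anyone has seen the baseline results. A revascularisation happens because a doctor decides on it, and here the treating doctor may hold the very result that the analysis tests as a predictor. If an abnormal finding leads to further investigation and then to an elective procedure, the record check will confirm the procedure as a valid event. Nothing stated in the article separates it from an event caused by progressing disease.

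The hazard ratio for that finding would then mix two things: how well it predicts disease, and how doctors respond to it. What is at stake is the stated aim of judging how much subclinical damage adds to vascular risk. About 10% of participants are expected to have infarcts, so the exposed group is small and a few procedures can move the estimate.

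**Working it through.** **The plan's own figure.** Statistical methods gives at least 865 participants for an expected prevalence of 10%, 95% confidence and an accuracy of 2 points. The formula n = z² × p(1 − p) / d² gives 1.96² × 0.10 × 0.90 / 0.02² ≈ 864.3, rounded up to 865. The figure reproduces. It sizes the prevalence aim and does not bear on this point; only the 1000 participants and the 10% prevalence are used below.

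**Inputs.**
- From the article: 1000 participants and 10% with infarcts, so about 100 carriers and 900 non-carriers; follow-up of at least 3 years.
- Assumed, because the article gives no figure: a true 3-year risk r of the cardiovascular endpoint, equal in both groups; and k procedures among the 100 carriers that disclosure prompted, with none among non-carriers.

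**Formula.** Risk ratio = ((100r + k) / 100) / r.

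With r = 3%, carriers have 3 + k events and non-carriers have 27 of 900:

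| k | Carriers | Risk ratio | Fisher p |
|---|---|---|---|
| 0 | 3/100 | 0.03/0.03 = 1.0 | 1.00 |
| 1 | 4/100 | 0.04/0.03 = 1.33 | 0.54 |
| 2 | 5/100 | 0.05/0.03 = 1.67 | 0.24 |
| 3 | 6/100 | 0.06/0.03 = 2.0 | 0.13 |

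On the hazard scale, HR = ln(1 − r − k/100) / ln(1 − r) gives 1.34, 1.68 and 2.03 for k = 1, 2 and 3.

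**Range over the assumed base risk.** For k = 1 to 3, the risk ratio runs from 1.5 to 2.5 at r = 2% and from 1.2 to 1.6 at r = 5%.

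**Chance of a misleading result.** At r = 3% and k = 3 there are 33 events in all. The Schoenfeld approximation with 10% exposed uses √(33 × 0.1 × 0.9) × ln 2.03 = 1.22. The probability of p < 0.05 is then Φ(1.22 − 1.96) ≈ 23%, and of passing the p < 0.1 screen Φ(1.22 − 1.645) ≈ 34%. At k = 1 these fall to about 7% and 12%.

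**The opposing route.** If preventive treatment prompted by the same summary avoided one event among carriers while one procedure was prompted, the ratio would be ((3 − 1 + 1)/100) / (27/900) = 1.0. The two reactions to disclosure can cancel, or either can dominate.

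**The case against.** The case on the other side is substantial.

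- **The wording implies need.** For limbs, aorta and carotids, the text counts complications that require revascularisation, not every procedure. A reader might infer that any elective procedure would count although nothing clinical had happened; the text does not say that. The qualifier narrows the problem without closing it, since the need is judged by doctors who may know the baseline findings. Coronary angioplasty or surgery carries no such qualifier.
- **The carotid route is not in the document.** A reader might infer that a disclosed infarct leads to carotid imaging and then to a procedure. No carotid imaging is listed at baseline, and the stated advice is medical: "recommendations will be to optimize BP control in all cases as much as possible", with drug treatment to be considered at high estimated risk. No work-up or referral is mentioned.
- **Disclosure of ABI is an inference.** The article says how the value is derived ("The lowest of the right and left ABI values will be used") but not that it is sent. Disclosure of infarcts is strongly implied, because advice on them follows in the same paragraph.
- **The contrast is not clean.** Summaries go out for every participant, and someone without infarcts may have another abnormal result that prompts action.
- **The direction is open.** A reader might infer that the contribution of subclinical damage will be overstated. The reaction the article actually describes is preventive treatment, which could lower events in carriers.
- **The size is assumed.** The ratios restate the chosen rates, zero prompted procedures is a possible value, and even k = 3 gives a 95% interval for the risk ratio of about 0.85 to 4.7.

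All of this limits the point. What remains is that results go to the doctors whose decisions can generate part of the endpoint, and those findings are then tested against it. This concerns how the article defines the endpoint, not a detail left to an analysis plan.

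**Conclusion.** The point holds as a possible bias in a secondary endpoint. Procedures prompted by disclosed findings could inflate the association of silent infarcts with cardiovascular events, and that of ABI if the summary includes it. Preventive treatment prompted by the same summary could reduce it, so the net direction cannot be stated. Stroke/TIA, the primary longitudinal outcome, is not inflated by this route, and lesion prevalence is measured before any disclosure.

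The article supports no estimate of size. With 100 carriers and an assumed 3% risk in both groups, ratios of 1.0 to 2.0 correspond to 0 to 3 prompted procedures. This shows only that the estimate is sensitive to a handful of procedures. Disclosure itself is not an error and need not change. The point merits a low-cost improvement to the endpoint and calls no stated figure into question.

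**What to change.** At the record check already planned under Follow-up visits, record for each revascularisation whether it followed new symptoms or an acute event after baseline. This should be an objective criterion read from the records, where feasible by someone unaware of the baseline MRI and ABI. It should not ask whether the study prompted the procedure, because that causal judgement could itself add bias.

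Under Study outcome, add a restricted cardiovascular endpoint consisting of myocardial infarction, hospitalised angina, heart failure admission, symptom-driven revascularisation and vascular death. Report it alongside the full composite. If the two give similar hazard ratios, prompted procedures are an unlikely explanation; if they differ, the reader can see it. The restricted endpoint does not remove any effect of preventive treatment prompted by disclosure, which should be acknowledged when the results are interpreted.

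The cost is one extra field in the record check and one further analysis, with no new visits or participants and no change to care. The downside is fewer events, and so less precision, in the restricted endpoint.

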### Substudies (case–control studies nested in the ISSYS cohort)

#### Twenty-four hour ambulatory blood pressure monitoring (ABPM)

A nested case–control study within the ISSYS cohort will be performed with 24-hour ambulatory BP monitoring. Cases will be considered as participants in whom silent brain infarctions are detected versus controls (participants with no brain infarctions). Cases will be matched with controls by age, gender, other vascular risk factors and antihypertensive treatment in a ratio of 1 to 2/ 1 to 3.

Oscillometric ABPM measurements will be obtained using a Spacelabs 90217-5Q device (Spacelabs Healthcare, Issaquah, Washington, USA), validated according to the protocol of the British Hypertension Society [25]. The BP measurements will be made every 20 minutes during daytime and every 30 minutes during sleeptime in a day of standard activity and with a cuff suited to the size of the patient’s arm. All recordings with at least 70% of valid readings or at least 45 measurements will be considered for the analysis.

Daytime ambulatory hypertension will be defined as a mean daytime BP ≥ 135/85 mmHg and sleeptime ambulatory hypertension as a mean BP ≥ 120/70 mmHg, according to the ESH Guidelines(1).

Circadian BP patterns will be assessed, considering a nondipping status as a night to day ratio of mean systolic blood pressure (SBP) of 0.9 or more. Also the sleep-through morning surge defined as the morning BP (2-hour average of four 30-minute BP readings just after wake-up) minus the lowest nocturnal BP (1-hour average of the 3 BP readings centered on the lowest night-time reading) will be calculated [26].

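### ABPM substudy: the morning-surge definition does not fit the 20-minute daytime schedule, and the recording-validity rule does not secure the night readings that three of the four measures need

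*Protocol article*

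**What the plan says.** All the relevant rules stand in one section of the protocol article, on twenty-four hour ambulatory blood pressure monitoring, under the substudies.

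- Schedule: "The BP measurements will be made every 20 minutes during daytime and every 30 minutes during sleeptime".
- Acceptance of a recording: "All recordings with at least 70% of valid readings or at least 45 measurements will be considered for the analysis". No separate requirement is given for day or night.
- Morning term of the surge: "2-hour average of four 30-minute BP readings just after wake-up".
- Nocturnal term of the surge: "1-hour average of the 3 BP readings centered on the lowest night-time reading".
- Other measures that use night readings: "sleeptime ambulatory hypertension as a mean BP ≥ 120/70 mmHg", and dipping, "considering a nondipping status as a night to day ratio of mean systolic blood pressure (SBP) of 0.9 or more".

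The section does not say how many hours count as daytime or as sleeptime.

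**The concern.** There are two separate points.

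The first is an inconsistency. Readings taken just after waking are daytime readings, so they come 20 minutes apart. A rule that asks for four readings 30 minutes apart over two hours describes a series that this schedule does not produce. The analyst must then decide which part of the definition to keep, and that choice would be made with the data in hand.

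The second is a gap in a rule that the article does fix. Acceptance depends on a count over the whole recording, and most scheduled readings fall in the day. Good daytime data can therefore carry a recording over the threshold with few or no night readings. Sleeptime hypertension, dipping status and the morning surge all need night data; of the four measures defined, only daytime hypertension does not. With no night readings these three are missing. With a handful they can be calculated only from a thin sample of the night, if at all.

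**Working it through.** **Inputs.** Spacing of 20 minutes by day (3 readings an hour) and 30 minutes in sleep (2 an hour), the 70% and 45-reading thresholds, and the surge definition all come from the ABPM section. The length of the day, D hours, is not given. I take 16 hours as the base case and 12 to 18 hours as the range; this is an assumption.

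**Morning term.**

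- Readings in two hours at daytime spacing: 120 / 20 = 6, at 20, 40, 60, 80, 100 and 120 minutes.
- A 30-minute series would fall at 30, 60, 90 and 120 minutes. Only 60 and 120 are common to both.
- Four consecutive scheduled readings cover 4 × 20 = 80 minutes, a third less than 120.

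Four readings, 30-minute spacing and a 2-hour window therefore cannot all hold on this schedule.

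**Nocturnal term.** Three readings at 30-minute spacing run from 30 minutes before the central one to 30 minutes after it, which is one hour. This half is consistent.

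**Validity rule: reproducing the stated 45.** Scheduled readings = 3D + 2(24 − D) = D + 48. At D = 16 this is 48 + 16 = 64, and 0.70 × 64 = 44.8, which rounds up to 45. The plan's figure is reproduced, so the two thresholds agree with each other and with the schedule in the base case.

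**Validity rule: what it admits.** Because the two criteria are joined by *or*, the fewest valid readings that pass is the smaller of 45 and 70% of the total (rounded up). Suppose all daytime readings are valid:

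| Day (h) | Day slots | Night slots | Total | 70%, rounded up | Fewest that pass | Night readings needed |
|---|---|---|---|---|---|---|
| 12 | 36 | 24 | 60 | 42 | 42 | 6 |
| 13 | 39 | 22 | 61 | 43 | 43 | 4 |
| 14 | 42 | 20 | 62 | 44 | 44 | 2 |
| 15 | 45 | 18 | 63 | 45 | 45 | 0 |
| 16 | 48 | 16 | 64 | 45 | 45 | 0 |
| 18 | 54 | 12 | 66 | 47 | 45 | 0 |

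Daytime readings alone meet the 70% criterion when 3D ≥ 0.70(D + 48), that is 2.3D ≥ 33.6, or D ≥ 14.6 hours. They meet the 45-reading criterion when 3D ≥ 45, or D ≥ 15 hours. In the base case 48 of 64 is 75%, so both are met, and three daytime readings could even be lost (48 − 45 = 3).

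Across the range the rule never requires more than 6 of 24 night readings, a quarter, when the daytime is complete. At 14 hours the two that suffice are fewer than the three needed for the nocturnal term.

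**The case against.** The strongest reply is that a journal article condenses a fuller protocol, and a minimum for each period of the day is the kind of detail left to that document. The text also says only that a qualifying recording is considered for analysis, not that it will supply every measure. This has some force: the validity rule contradicts nothing. But the article states a specific acceptance rule next to measures that depend on the night, and the rule as written admits recordings that cannot supply them. That is a weakness in what is fixed, not just an absence.

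On the morning term, one could say that a 30-minute reading means a 30-minute average, or that the monitor is still at its night interval after waking. Either would soften the mismatch, but the text says neither.

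It is also fair that the zero-night recording is an extreme case. At a 16-hour day it needs at least 45 of 48 daytime readings valid (94%) and none of 16 at night, and nothing in the article suggests how often that would happen. Cases and controls share the device, the schedule and the rule, so there is no stated reason for the loss to differ between them.

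Four stronger readings are tempting and are not supported:

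- That the ABPM rules as a whole contradict the schedule. Only the morning term does.
- That the surge cannot be computed. The 2-hour window is stated, and six scheduled readings fall in it.
- That recordings without night readings always qualify. On complete daytime data this fails at a day of 14 hours or less.
- That the case–control contrast is biased or weakened by a known amount. The article gives nothing from which to estimate this.

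**Conclusion.** Both points hold, with limited reach. The morning half of the surge definition is inconsistent with the stated schedule: six readings fall in the window, not four. This needs no assumption beyond treating readings after waking as daytime readings.

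The validity rule agrees with the schedule but leaves the night unprotected. How far depends on the assumed day length: with complete daytime data, no night readings are needed from about 14.6 hours upward, and between 2 and 6 are needed at 14 down to 12 hours. How many recordings would be affected, and by how much any measure would shift, cannot be derived from the document.

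The consequence is confined to the sleeptime, dipping and surge measures of one nested substudy. The daytime mean, the primary outcomes and the sample-size calculation are untouched. It is worth correcting because the correction costs so little.

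**What to change.** Two definition lines in the substudy plan, settled before the ABPM data are analysed:

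1. Define morning BP as the mean of all valid readings in the two hours after waking (six scheduled). Leave the nocturnal term as it is.
2. Keep the whole-recording rule for the daytime mean. For the sleeptime mean, the night-to-day ratio and the surge, also require a pre-stated minimum of valid sleeptime readings. One option is to apply the existing 70% to sleeptime alone; with 16 night slots that is 0.70 × 16 = 11.2, so 12 readings. Other minimums are defensible, provided the number is fixed in advance.

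Neither the recording schedule nor the device setting has to change. The cost is that recordings with sparse night data drop out of the night-based measures, and only those; the number excluded from each measure should be reported for cases and for controls.
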